##### **11.1.5.1. Hematology**

Hematology laboratory assessments will be performed at screening pre-run in, 6 hours post dose on Day 0, on day 14 and at each monthly follow-up visit, including the EOS visit. Hematology lab assessments include WBC, absolute and percent differential WBC, platelet count, RBC, hemoglobin, reticulocyte number and percent.

##### **11.1.5.2. Blood Chemistry**

Chemistry laboratory tests will be performed at screening pre-run in, 6 hours post dose on Day 0, on day 14, and at each monthly follow-up visit, including the EOS visit. Each test will include blood glucose, creatinine, uric acid, blood urea nitrogen (BUN), sodium, potassium, chloride, calcium, phosphorus, total protein, albumin, globulin, total bilirubin, direct bilirubin, alkaline phosphatase, lactate dehydrogenase (LDH), aspartate aminotransferase (AST or SGOT), alanine aminotransferase (ALT or SGPT), and C-reactive protein (using a high-sensitivity assay).

##### **11.1.5.3. Urinalysis and Urine Protein/Creatinine Ratio**

Urine will be collected as clean-catch at screening run-in, day 14 and EOS. Urinalysis will be performed by dip test and, if abnormal, microanalysis will be performed.

#### **11.1.5.4. Coagulation**

Coagulation assessments as a safety measure will be measured by PT and aPTT and will be performed according to [Table 3](#) and at the same time points as Hematology ([11.1.5.1](#)). Platelet measurements will be done routinely for safety as part of a complete blood count.

Additional measurements coagulation assessments and measures of endothelial activation will be performed, but these will be exploratory analysis only, and not be analyzed as part of the safety evaluation.

#### **11.1.5.5. Pregnancy Screen**

Women of child-bearing potential will be screened for pregnancy at screening pre-run-in (blood test) and prior to administration of study drug (urine test). If the results of the serum pregnancy test at screening pre-run-in are positive, the subject will be excluded. Prior to dosing on Day 0, a urine pregnancy test will be performed to confirm the female subject is not pregnant. If the urine pregnancy test is positive, then the subject will be withdrawn from the study. Results of the pregnancy tests must be recorded in the subject's source documents (medical chart).

### **11.2. Adverse and serious adverse events**

#### **11.2.1. Definition of adverse events**

##### **11.2.1.1. Adverse event (AE)**

An AE is the development of an undesirable medical condition or the deterioration of a pre-existing medical condition following or during exposure to a pharmaceutical product, whether or not considered casually related to the product. In clinical studies, an AE can include an undesirable medical condition occurring at any time, including baseline or washout periods, even if no study treatment has been administered.

**Event of interest (EOI) criteria:** an EOI is defined only for adverse events that occur within 2 weeks of dosing (with the exception of any acute vaso-occlusive episode). Any adverse event grade 3 or higher on NCI CTCAE version 4.03 will be considered an EOI, and a determination of whether it constitutes a DLT will be made by the SRC.

All baseline signs and symptoms and AEs that occur after any subject has been enrolled, before treatment, during treatment, or for 30 days following the recovery of iNKT cells, whether or not they are related to the study, must be recorded on forms provided by NKTT.

##### **11.2.1.2. Serious adverse event (SAE)**

A serious adverse event is an AE occurring during any study phase (i.e., baseline, treatment, washout, or follow-up), and at any dose of the investigational product, comparator or placebo, that fulfills one or more of the following:

- Results in death
- It is immediately life-threatening
- It requires in-subject hospitalization or prolongation of existing hospitalization
- It results in persistent or significant disability or incapacity

- Results in a congenital abnormality or birth defect
- It is an important medical event that may jeopardize the subject or may require medical intervention to prevent one of the outcomes listed above.

All SAEs that occur after any subject has been enrolled, before treatment, during treatment, or within 30 days following the recovery of iNKT cells, whether or not they are related to the study, must be recorded on forms provided by NKT Therapeutics Inc.

#### **11.2.1.3. Other adverse event (OAE)**

OAEs will be identified by the Drug Safety Physician during the evaluation of safety data for the Clinical Study Report. Significant adverse events of particular clinical importance, other than SAEs and those AEs leading to discontinuation of the subject from the study, will be classified as OAEs. For each OAE, a narrative may be written and included in the Clinical Study Report.

### **11.3. Relationship to study drug**

An Investigator who is qualified in medicine must make the determination of relationship to the investigational product for each AE (Unrelated, Possibly Related or Probably Related). The Investigator should decide whether, in his or her medical judgment, there is a reasonable possibility that the event may have been caused by the investigational product. If no valid reason exists for suggesting a relationship, then the AE should be classified as “unrelated.” If there is any valid reason, even if undetermined, for suspecting a possible cause-and-effect relationship between the investigational product and the occurrence of the AE, then the AE should be considered “related.”

If the relationship between the AE/SAE and the investigational product is determined to be “possible” or “probable” the event will be considered to be related to the investigational product for the purposes of expedited regulatory reporting.

For the purposes of this study, a disease-specific adverse event is an adverse event or outcome that is associated with SCD. Examples include, but may not be limited to: hemolysis, hepatic/splenic sequestration, haptoglobin decrease, hemoglobinuria, pain crisis, bone pain, chest wall pain, pain in extremity, priapism in men, acute chest syndrome, gall-stones, leg ulcers, avascular necrosis of bone, stroke, cognitive disabilities. These events will be captured as AE and/or SAEs in the CRF. Disease specific AEs not thought to be related to NKTT120 will not be considered dose-limiting events.

### **11.4. Recording adverse events**

Adverse events spontaneously reported by the subject and/or in response to an open question from the study personnel or revealed by observation will be recorded during the study at the investigational site. Clinically significant changes in laboratory values, blood pressure, and pulse need not be reported as AEs. However, abnormal values that constitute an SAE must be reported and recorded as an AE. Information about pre-existing signs and symptoms will be collected from the time the subject signs an informed consent form. AEs will be collected from the first administration of study drug until the end of the study. SAE information will be collected from administration of study drug until their EOS visit, which is 30 days following the recovery of iNKT cells in the peripheral circulation. The AE term should be reported in standard medical

terminology when possible. For each AE, the investigator will evaluate and report the onset (date and time), resolution (date and time), intensity, causality, action taken, serious outcome (if applicable), and whether or not it caused the subject to discontinue the study.

Intensity will be assessed according to the CTCAE grading scale version 4.03.

It is important to distinguish between serious and severe AEs. Severity is a measure of intensity whereas seriousness is defined by the criteria in Section 11.2.1.2. An AE of severe intensity may not be considered serious.

In principle, pregnancy and the lactation period are exclusion criteria for clinical studies involving investigational drugs that are not directly related to the respective conditions. Should a pregnancy occur during this study, it must be reported and recorded on the pregnancy form and the subject should be followed in the study until one month after recovery of iNKT cells and during the entire course of the pregnancy and postpartum period. All recommendations described in the [Investigator Brochure](#) pertaining to pregnancy and lactation must be carefully considered. Pregnancy in itself is not regarded as an AE unless there is a suspicion that an investigational product may have interfered with the effectiveness of a contraceptive medication.

The outcome of all pregnancies (spontaneous miscarriage, elective termination, normal birth or congenital abnormality) must be followed up and documented even if the subject was discontinued from the study.

All reports of congenital abnormalities and birth defects are SAEs. Spontaneous miscarriages should also be reported and handled as SAEs. Elective abortions without complications should not be handled as AEs.

## **11.5. Reporting adverse events**

All SAEs (related and unrelated) will be recorded from the or first administration of study drug until the EOS visit. Any SAEs considered possibly or probably related to the investigational product and discovered by the Investigator at any time after the study should be reported. All SAEs must be reported to the CRO within one business day of the first awareness of the event.

Additional follow-up information, if required or available, should all be faxed to the CRO within one business day of receipt and this should be completed on a follow-up SAE form and placed with the original SAE information and kept with the appropriate section of the CRF and/or study file.

NKTT is responsible for notifying the relevant regulatory authorities of reportable events. It is the Principal Investigator's responsibility to notify the IRB of all SAEs that occur at his or her site. Investigators will also be notified of all unexpected, serious, drug-related events (7/15 Day Safety Reports) that occur during the clinical trial. Each site is responsible for notifying its IRB of these additional SAEs.

## 12. STATISTICS

The primary endpoint of this study is the identification of a safe and tolerable IV dose of NKTT120 in subjects with SCD to be taken forward in phase 2 studies of SCD subjects.

Secondary endpoints of this study are laboratory assessments based on peripheral blood to evaluate the PK of NKTT120 and to identify iNKT cell numbers and markers of activation. Pulmonary function, immunogenicity profile, QoL domains, use of analgesics, and pain score profile in subjects receiving NKTT120 will also be examined. For all studies, serial changes from baseline within subjects will be evaluated.

Subjects who sign informed consent, completed all pre-screening requirements and were determined to be eligible, but are not dosed, will be replaced.

Subjects who are enrolled and dosed will define the Safety Population.

Subjects, who are enrolled, dosed, and complete the two week evaluability period for DLTs, will define the DLT-evaluable population.

Completed subjects are defined as those subjects who continue to return to the clinic for visits until their iNKT cells recover and return for their EOS visit.

### Escalation scheme

Five dose levels of NKTT120 will be assessed. Each dose level will be administered as a single ascending IV dose. The dose levels to be investigated are 0.001, 0.003, 0.01, 0.03 and 0.1 mg/kg.

A standard dose escalation Fibonacci 3+3 design will be employed. Initially, three subjects will be treated. If no subject experiences DLT, dosing will escalate. If one subject experiences DLT, 3 additional subjects will be treated at the current dose and escalation will occur only if no more than 1 of 6 subjects experiences DLT. If  $\geq 2$  of 3 - 6 subjects experiences DLT at the initial dose level of 0.001 mg/kg, then it may be de-escalated. The study continues until MTD has been determined, or the highest dose cohort is filled. If no MTD is reached, RDL will be determined based on the overall safety profile of NKTT120 and the duration of iNKT cell depletion. The RDL(s) for phase 2 will be determined by a dose that is at or below the highest dose tested which is associated with timing of iNKT cell recovery that allows dosing every 4-6 months in phase 2 studies. The dose-level cohort that represents the RDL will be expanded to 6 subjects to confirm the RDL. [Table 5](#) below provides the probability of dose escalation.

**Table 5: Statistical Properties of the Study Design**

| True but unknown probability of DLT | DLT  | Pr(escalate) |
|-------------------------------------|------|--------------|
|                                     | 0.05 | 0.973        |
|                                     | 0.10 | 0.906        |
|                                     | 0.15 | 0.814        |
|                                     | 0.20 | 0.709        |
|                                     | 0.25 | 0.600        |
|                                     | 0.30 | 0.494        |
|                                     | 0.40 | 0.309        |
|                                     | 0.50 | 0.172        |
|                                     | 0.80 | 0.009        |
|                                     | 0.09 | 0.001        |

DLTs are defined as in 6.6.1. Subjects will be observed for 2 weeks following dosing to fully assess DLT (with the exception of any acute vaso-occlusive episode).

### Analysis of Secondary Endpoints

Demographics and baseline status will be documented by dose level and/or overall, as applicable.

### 12.1. Pharmacokinetics and pharmacodynamics

Non-compartmental pharmacokinetic parameters ( $C_{max}$ ,  $C_{min}$ ,  $C_{avg}$ , AUC,  $t_{1/2}$ ,  $V_d$ ) will be calculated for all subjects. Descriptive statistics of these parameters will be provided by dose level.

Descriptive statistics of the PK/PD (peripheral iNKT cell:T cell ratio, depletion and recovery to quantifiable levels) will be provided by dose level. PK/PD will be correlated/associated with AEs, pain scores and other diary endpoints, and changes in biomarkers.

Binary criteria have been established for activity for the secondary endpoints. Decrease in iNKT cell number and/or markers of activation by 75% will be examined to assess the impact of infusional NKTT120 on these endpoints. These results will be presented as point estimates of proportion of subjects achieving target reduction, with 90% exact binomial confidence intervals, for subjects within each of the dose level cohorts of the study. Mixed models will also be explored to elucidate the tempo of changes in iNKT cell number and markers of activation, controlling for subject and for cohort of study as well as other potential covariates.

### 12.2. Clinical measures of SCD and biomarker analysis

Changes in leukocyte counts, hemoglobin, reticulocytes, platelets, LDH, and CRP for each subject will be compared to baseline values and changes will be presented as change tables and described.

Changes from baseline in serum concentrations of IFN $\gamma$ , TNF $\alpha$ , IL-1 $\beta$ , IL-6, IL-8, F1+2, D-dimers, vWF, sPLA $_2$  and sP-selectin will be presented as change score.

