#### **Statistical methods:**

Primary outcome: Maximum tolerated dose (MTD) is defined as the dose level that is estimated to produce DLT in < 33% of subjects in a cohort using a 3+3 design. If no MTD is achieved, the RDL will be determined based on the overall safety profile of NKTT120 and the duration of iNKT cell depletion.

Secondary outcome: Non-compartmental pharmacokinetic parameters--peak concentration ( $C_{max}$ ), minimum concentration ( $C_{min}$ ), average concentration ( $C_{avg}$ ), area under the time-concentration curve (AUC), half-life ( $t_{1/2}$ ), volume of distribution ( $V_d$ )--will be calculated for all subjects. Descriptive statistics of these parameters will be provided by dose level.

Descriptive statistics of the PK/PD (peripheral iNKT cell subset/T cell (TC) ratio depletion and recovery to quantifiable levels) will be provided by dose level. PK/PD will be examined for association with AEs, pain scores and other endpoints, and changes in biomarkers.

Demographics and baseline status will be documented by dose level and/or overall, as applicable.

Descriptive statistics of change in pain score, analgesic use, peak expiratory flow, and shortness of breath will be collected by eDiary and/or during clinic visits. The Quality of Life (QoL) assessments will be collected at clinic visits and will be compared to pre-treatment screening run-in values. Trends in improvement or deterioration in these values with treatment and across the dose-level cohorts will be described.

Descriptive statistics of change from screening in serum and cellular biomarkers of inflammation, coagulation, and endothelial function will be provided.

ADAs will be described as present or absent and correlated with NKTT120 serum concentrations and iNKT cell recovery. Numbers of subjects with positive tests for ADAs per cohort and per study will be reported.

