| SPLA 2               | Secretory phospholipase A 2                                                                                                                 |
| sP-selectin                     | sP-selectin - A soluble plasma/serum form of P-selectin released from platelets and endothelial cells                                                  |
| SRC                             | Safety review committee                                                                                                                                |
| t 1/2                | Half life                                                                                                                                              |

| Abbreviation or Specialist Term | Definition                         |
|----------------------------------------|-------------------------------------------|
| TB                                     | Tuberculosis (Mycobacterium tuberculosis) |
| TIA                                    | Transient ischemic attack                 |
| TNF $\alpha$                           | Tumor necrosis factor alpha               |
| TRV                                    | tricuspid regurgitant jet velocity        |
| ULN                                    | Upper limit of normal                     |
| V d                         | Volume of distribution                    |
| Vol                                    | Volume                                    |
| vWF                                    | Von Willebrand Factor                     |
| WBC                                    | White blood cell (leukocyte)              |

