### **5.2. Secondary objectives**

1. To assess the PK profile of IV NKTT120
2. To assess the PD profile of peripheral iNKT cell depletion and recovery following IV NKTT120, including the recovery of the population of activated iNKT cells as measured by the expression of CD 69.
3. To evaluate change in clinical measures of SCD activity (e.g., leukocyte counts, Hgb, reticulocytes, platelets, LDH, hsCRP)
4. To evaluate the effect of NKTT120 on daily pain and use of analgesic medication compared to screening values (e.g., 2-week screening run-in daily pain score and analgesic use)
5. To evaluate the effect of the administration of NKTT120 on AHR comparing PFTs (including FVC, FEV1, FEF25-75%) and PEF to screening values
6. To evaluate changes in QoL and pain compared to screening values (ASCQ-Me, PROMIS short-form and eSCaPe e-Diary).
7. To explore a number of serum and cellular biomarkers of inflammation, coagulation and endothelial function (e.g. IFN $\gamma$ , TNF $\alpha$ , IL1 $\beta$ , IL-6, IL-8, sPLA2, sP-selectin, F1+2, D-dimers and vWF) compared to screening values
8. To evaluate anti-drug antibodies (ADAs) following single dosing

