#### **6.3.2.2. Biologic activity endpoints and biomarker activity**

The following endpoints will be used to determine the biologic activity of NKTT120:

- Changes in clinical measures of SCD activity, including changes from baseline in leukocyte counts, hemoglobin, reticulocytes (number and percentage of RBCs), platelet count, LDH, and CRP
- Change in pain frequency and intensity and use of analgesics compared to screening run-in from daily eDiary
- Changes in pulmonary function assessed at clinic visits as follows: forced vital capacity (FVC), forced expiratory volume in one second, forced expiratory flow rate at 25% to 75% of FVC (FEF25-75), peak expiratory flow rate, total lung capacity compared to screening run-in values

- 
- Changes in QoL domains defined by PROMIS short-form and ASCQ-Me domains, compared to screening run-in

The effect of iNKT cell depletion on biomarkers of inflammation, coagulation and endothelial activation will be explored by assessing changes from baseline in serum IFN $\gamma$ , TNF $\alpha$ , IL-1 $\beta$ , IL-6, IL-8, F1+2, D-dimers, vWF, sPLA2 and sP-selectin.

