| Evaluations                                                                     | Screening
pre-run-in
(4 weeks prior
to dosing) | Screening
run-in
(2 weeks prior
to dosing) | Day 0 (Dosing)                 |                                                   | Follow-up             |                       |                                        |
|---------------------------------------------------------------------------------|---------------------------------------------------------|-----------------------------------------------------|--------------------------------|---------------------------------------------------|-----------------------|-----------------------|----------------------------------------|
|                                                                                 |                                                         |                                                     | Pre-dose                       | Time
Post-dose                                 | Days
1,2,3,7,14    | Months
1,2,3, etc. | EOS 1 month post iNKT
cell recovery |
| Blood for peripheral lymphocytes
by flow cytometry (FACS) assay g | X                                                       | X                                                   | X                              | X
t= 6 hr                                      | X
1,2,
7, 14    | X
1,2,3, etc.      | X                                      |
| Blood for serum and cellular
biomarkers h                         |                                                         |                                                     | X                              | X
t = 6 hrs                                    | X
7, 14            | X
1,2,3, etc.      | X                                      |
| Serum for PK i                                                       |                                                         |                                                     | X                              | X
t= 15 min,
30 min, 1
hr, 3 hr, 6
hr | X
1,2, 3,
7, 14 | X
1,2,3, etc.      | X                                      |

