|------------------------------|---------------------------------------------------------|-----------------------------------------------------|----------------|-------------------|--------------------|-----------------------|----------------------------------------|
|                              |                                                         |                                                     | Pre-dose       | Time
Post-dose | Days
1,2,3,7,14 | Months
1,2,3, etc. | EOS 1 month post iNKT
cell recovery |
| Administration of study drug |                                                         |                                                     |                | X
t = 0        |                    |                       |                                        |

a Should ensure subject meets all inclusion criteria and no exclusion criteria

b SCD history includes frequency of vaso-occlusive crisis, history of acute chest syndrome, other known organ involvement/damage, history of transfusions, recent transfusions

c Immunization history, see Section 18.1

d Just prior to dosing, on Day 0, then every 15 minutes post dose for 1 hour or until stable, then every 30 minutes post infusion.

e PA and lateral to rule out TB or other pulmonary disease process

f Blood glucose, creatinine, uric acid, blood urea nitrogen (BUN), sodium potassium chloride, calcium, phosphorus, total protein, albumin, globulin, total bilirubin, direct bilirubin, alkaline phosphatase, lactic acid dehydrogenase (LDH), aspartate aminotransferase (AST or SGOT), alanine aminotransferase (ALT or SGPT) and CRP

g iNKT cell subsets, NK cells, total T lymphocytes, B cells, iNKT cell activation marker (CD69)

h INF $\gamma$ , F1+2, D-dimers, vWF and cytokines including INF $\gamma$

i Two aliquots for PK should be prepared (one for current analysis and one for retained). Retained samples may be used to re-test PK at end of study or for other serum test such as autoantibodies, serum cytokines or other tests required to evaluate AEs or mechanism of action of NKTT120.

j If dip is abnormal, proceed to microanalysis.

k Serum pregnancy test will be performed at screening pre-run-in and urine pregnancy test at Day 0 just prior to dosing.

l Will be administered in clinic prior to any other assessments. Instruments include PROMIS and ASCQ-Me

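### With serum as the specimen, the F1+2 change score would mainly measure clotting in the tube, and sP-selectin would carry platelet release

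*Protocol*

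**What the plan says.** Section 6.3.2.2 states that effects on inflammation, "coagulation and endothelial activation will be explored by assessing changes from baseline in serum" levels of ten analytes: IFNγ, TNFα, IL-1β, IL-6, IL-8, F1+2, D-dimers, vWF, sPLA2 and sP-selectin. Section 12.2 repeats the list as "Changes from baseline in serum concentrations of" these analytes and ends "and sP-selectin will be presented as change score".

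The objective and the synopsis use a similar label. Secondary objective 7 in section 5.2 is "To explore a number of serum and cellular biomarkers of inflammation, coagulation and endothelial function", and the statistical methods in the synopsis promise "Descriptive statistics of change from screening in serum and cellular biomarkers of inflammation, coagulation, and endothelial function will be provided".

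Table 3 has one row for this draw, "Blood for serum and cellular" biomarkers, at Day 0 pre-dose, 6 hours, Days 7 and 14, monthly and end of study. Its footnote h ties "F1+2, D-dimers, vWF and cytokines including" IFNγ to that row.

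The only mention of plasma for any of these analytes is the abbreviation entry for sP-selectin in Table 2: "A soluble plasma/serum form of P-selectin released from platelets and endothelial cells". No section assigns any of the ten to an anticoagulated sample.

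**The concern.** Serum is the fluid left after blood has clotted. That matters little for an analyte that clotting neither makes nor releases, but it matters for two on this list.

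- **F1+2.** The protocol does not spell the term out. It is prothrombin fragment 1+2, released when prothrombin is converted to thrombin. Clotting the sample is that conversion, so preparing the specimen produces the analyte.
- **sP-selectin.** The protocol's own definition names platelets as a source, and platelets are activated while a sample clots. A serum value therefore mixes what circulated with what the platelets released in the tube.

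Secondary objective 7 asks whether iNKT depletion changes coagulation and endothelial function. Section 5.3 plans to correlate the results with the PK/PD profile, and section 12.1 plans the same for biomarker changes. Platelet count is itself a tracked outcome in sections 6.3.2.2 and 12.2, so a change in platelets could look like a change in endothelial activation.

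The loss could not be repaired later. Each subject is dosed once, and the retained aliquots in Table 3 footnote i are PK serum, which cannot replace plasma.

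**Working it through.** There is no stated figure to reproduce. The biomarker analysis is descriptive, and no power, margin or error rate is at issue. The check compares the text with the planned metric.

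**1. Is serum really specified?** The analysis section (12.2) and the endpoint section (6.3.2.2) both say serum for the whole list. The synopsis, objective 7, section 5.3 and Table 3 say serum and cellular. Section 11.1.5.4 mentions additional coagulation and endothelial measurements without naming a specimen. The laboratory manual is cited in section 10.2 only for shipping PK serum. So serum is stated positively in the two sections that define and analyse the endpoint, and nothing in the protocol corrects it.

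**2. What does a tube artefact do to a change score?** Write measured value = in-vivo value + tube artefact. Then

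change in measured value = change in in-vivo value + change in artefact.

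An artefact that is constant within a subject cancels. One that varies between visits does not. If the two changes are independent and r = SD(change in artefact) / SD(change in in-vivo value), the artefact's share of the change-score variance is r² / (1 + r²). The documents give no value for r, so these are assumed values:

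| r (assumed) | Calculation | Share of variance from the tube |
|---|---|---|
| 0.5 | 0.25 / 1.25 | 20% |
| 1 | 1 / 2 | 50% |
| 3 | 9 / 10 | 90% |
| 10 | 100 / 101 | 99% |

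The table shows how the share depends on r. It does not estimate the share in this trial.

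**3. Which analytes are affected?**

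| Analyte | Relation to clotting in the tube | Effect on the serum change score |
|---|---|---|
| F1+2 | Generated by it | Dominated by the artefact, which varies with clotting time, handling and prothrombin |
| sP-selectin | Partly released from platelets | Contaminated to an unknown extent; can move with platelet count |
| D-dimers | Come from breakdown of cross-linked fibrin, not from clot formation alone | Not mainly created in the tube |
| vWF | Mainly circulating protein, with a platelet-released part | Not mainly created in the tube |

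Section 12.6 gives three to six subjects per cohort, so averaging within a cohort removes little of the added noise.

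**4. Where does Table 3 already have a coagulation sample?** PT and aPTT follow the hematology schedule (section 11.1.5.4): screening pre-run-in, 6 hours, Day 14, monthly and end of study. Compared with the biomarker row, Day 0 pre-dose and Day 7 have no coagulation sample. Blood is drawn at both for flow cytometry and PK. Day 0 pre-dose is the only biomarker sample before treatment, so every change score depends on it.

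**5. Does footnote h match the endpoint list?** It names IFNγ, F1+2, D-dimers, vWF and cytokines in general. It does not name sPLA2 or sP-selectin, which sections 5.2, 5.3, 6.3.2.2 and 12.2 all list.

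**The case against.** The strongest reply is that nothing decided in this trial depends on these values. Section 11.1.5.4 makes the additional coagulation and endothelial measures exploratory and keeps them out of the safety evaluation. The PK/PD correlation has no decision rule. This stands, and it limits the weight of the point.

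A second reply is that tube types usually belong in a laboratory manual, that one exists and is not shown, and that serum may be loose wording for soluble. The manual may well specify plasma. If so, sections 6.3.2.2 and 12.2 contradict it and still need correcting.

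Three stronger readings are tempting, and the documents do not support them:

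- A reader might infer that all four coagulation and endothelial markers are produced by clotting. For D-dimers and vWF that fails. The most that can be said is that they are best measured in the same coagulation sample.
- A reader might infer a fixed dilution of any drug effect, for example a true 30% fall showing as 15% when the tube adds as much as was circulating. That arithmetic needs a constant artefact and a percentage change. Section 12.2 plans a change score; read as a difference, a constant artefact cancels, and only variation does harm.
- A reader might infer from footnote h that sPLA2 and sP-selectin will not be assayed. The footnote repeats IFNγ and leaves the other cytokines to a general word, so it is shorthand. The mismatch is editorial.

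**Conclusion.** The point holds for two of the ten analytes. Followed as written, the protocol yields an F1+2 change score that mainly reflects variable thrombin generation in the tube and cannot be interpreted as a drug effect. It yields an sP-selectin change score with added noise and a possible dependence on platelet count. The corresponding part of objective 7 and its correlation with PK/PD are weakened to that extent. MTD, RDL, dose escalation and safety are unaffected.

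The conclusion rests on what serum and F1+2 are, on the protocol's own description of sP-selectin, and on the artefact varying between visits within a subject. Its size cannot be derived from the documents. The correction is worth making before samples are drawn, but the trial's primary purpose does not depend on it.

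**What to change.** In sections 6.3.2.2 and 12.2 and in Table 3 footnote h, name the specimen for each analyte:

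- anticoagulated, platelet-poor plasma for F1+2 and sP-selectin;
- D-dimers and vWF from the same plasma tube;
- serum kept for IFNγ, TNFα, IL-1β, IL-6, IL-8 and sPLA2.

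Relabel the Table 3 row so that it covers plasma as well as serum and cellular samples, and adjust the labels in the synopsis and sections 5.2 and 5.3. Add sPLA2 and sP-selectin to footnote h so that it matches the endpoint list. If the laboratory manual already specifies plasma, align the protocol with it.

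The change is not free. Sites must separate and store plasma at every biomarker time point, which a PT/aPTT sample does not by itself provide. An extra tube is needed at existing draws, at least at Day 0 pre-dose and Day 7. No extra visit or venipuncture is required.
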